## 3.2 Study population

**3.2.1- PRIMARY ENDPOINT**

To evaluate the safety of a rapid, ultrarapid and ultrarapid plus infusion of rituximab based on the percentage of grade 2/3 or higher infusion-related reactions in comparison with the administration of rituximab as per standard clinical practice at the standard rate of 400 mg/h.

Infusion-related reactions are defined as adverse events that occur in the first 24 hours after infusion of rituximab and which are considered to be related to infusion of the drug in the investigator's opinion.

Infusion-related reactions will be graded as the EORTC guidelines: Common Terminology Criteria for Adverse Events (CTCAE) Version 5.0 of EORTC (27 November 2017)

| **GRADE** | **REACTION** |
| --- | --- |
| Grade I: Mild | - - Transitory reaction   - Infusion not suspended   - No indication for intervention |
| Grade II: Moderate | - - Infusion suspended, with rapid recovery of symptoms after symptomatic treatment (e.g., antihistamines, NSAIDs, analgesia, volume support)   - Prophylactic medication for less than 24 hours |
| Grade III: Severe | - - Prolonged symptoms (e.g., slow response to symptomatic medication or suspension of infusion)   - Symptoms recur after initial improvement   - Hospitalisation indicated |
| Grade IV: Very severe | - - Life-threatening symptoms   - Urgent intervention indicated |
| Grade V: | - - Related death |

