# 4.- TRIAL DESIGN

**4.1.- Variables**

Primary variable:

-Percentage of grade 2/3 or higher infusion-related reactions for the rapid, ultrarapid and ultrarapid plus infusions in comparison with the administration of rituximab as per standard clinical practice at the standard rate of 400 mg/h.

** Infusion-related reactions are defined as adverse events that occur in the first 24 hours after infusion of rituximab and which are considered to be related to infusion of the drug in the investigator's opinion.*

Secondary variables:

- Grade of infusion-related reactions (1-5 as per CTCAE version 4.0) occurring in each study group.

- Time (in minutes) between the start of infusion and onset of the infusion-related reaction.

Other variables:

- Age (years)

- Sex (male/female)

- Infusion group (rapid, ultrarapid or ultrarapid plus)

- Treatment type (induction/maintenance)

- Therapy type (rituximab in monotherapy/combination therapy - specify the type of concomitant treatment: chemotherapy, radiotherapy, targeted therapy, etc.)

- Lymphoma type (specify diagnosis)

- Rituximab cycle number

- Blood pressure, temperature, oxygen saturation and heart rate before starting and after finishing rituximab infusion

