# 6.- SUBJECT TREATMENT

When the patient attends the haematology surgery and has tolerated the maximum intravenous administration rate for rituximab (400 mg/h) during the first or second infusion, they will be invited to participate in the study and will be given the informed consent. If the patient complies with all the inclusion criteria and none of the exclusion criteria, and decides to participate, they will be given an appointment to attend the day hospital for administration of their treatment cycle at the infusion rate being studied at that time.

Three successive intervention groups with different infusion rates (rapid, ultrarapid and ultrarapid plus) will be established. The procedure for each cohort will be considered to be safe if fewer than four mild to moderate infusion-related reactions occur in the 16 patients from the corresponding cohort (25% of reactions). The onset of one or more grade 2 or higher infusion-related reactions will imply that the cohort is not safe and the clinical trial will be suspended. Before commencing the next cohort, a haematology specialist not linked to Araba University Hospital Haematology Department will carry out a safety monitoring. This will involve an evaluation of all infusions performed, with access to the progress reports (medical and nursing) to determine whether a reaction has occurred and the grade thereof. In an attempt to minimise the influence of the investigator on the safety evaluation, the safety monitor will receive the progress reports after references to the grade of the infusion-related reaction contained in the electronic medical records have been censored.

Rituximab will be diluted in 250 mL provided the maximum concentration established in the summary of product characteristics (max. 4 mg/mL) is not exceeded. The rituximab dose will not be changed.

If the patient is receiving concomitant chemotherapy, this will be administered after rituximab once the absence of adverse reactions has been confirmed.

The interventions applied in each of the three study groups are described below:

RAPID INFUSION GROUP

Administration of the IV premedication half an hour prior to the infusion of rituximab as per the standard regimen; generally, dexchlorpheniramine 5 mg IV and paracetamol 1 g IV half an hour prior to rituximab.

The rituximab dose will then be administered at the standard dose: 375 mg/m^2^ diluted in 250 mL of saline over one hour, as follows:

- - - First 10 minutes at 450 mg/hour

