    - Probable: there is a reasonable time sequence between administration of the drug and onset of the adverse event. Said event coincides with the adverse reactions described for the drug, improves upon suspension of treatment and cannot be explained by other causes.
    - Possible: there is a reasonable time sequence between administration of the drug and onset of the adverse event. Said event coincides with the adverse reactions described for the drug but may be explained by other causes.
    - Conditional or improbable: there is a reasonable time sequence between administration of the drug and onset of the adverse event. Said event does not coincide with the adverse reactions described for the drug and can be explained by other causes.
    - Unrelated: there is no reasonable time sequence between administration of the drug and onset of the adverse event. Said event does not coincide with the adverse reactions described for the drug and can be explained by other causes.

For the purposes of expedited reporting, the categories definitive, probable and possible from the Karsch and Lasagna algorithm (1977) will be considered to be related and the category conditional or improbable will be considered to be unrelated.

The principal investigator at the research site, or a person designated by the PI, will be responsible for determining the possible relationship with the study treatment.

Serious Adverse Event (SAE) and Serious Adverse Reaction (SAR)

Any adverse reaction or adverse event which, at any dose:

- - - Causes the death of the patient.
    - Endangers the patient’s life.
    - Requires hospitalisation or prolongation of hospitalization of the patient.
    - Causes permanent or significant disability or incapacity.
    - Leads to a congenital anomaly/birth defect.

For reporting purposes, those suspected adverse events or adverse reactions considered to be important from a medical point of view will be considered to be serious even if they fail to comply with the above criteria, including important medical events requiring an intervention to prevent any of the consequences described above from occurring. Similarly, all suspected transmissions of an infectious agent via a drug will be reported as serious. The concept “serious”, defined above, should not be confused with “severe”, which refers to the severity of the AE or AR (mild/moderate/severe).

Suspected Unexpected Serious Adverse Reaction (SUSAR)

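### The outside monitor decides both whether a reaction occurred and its grade, but only grade is censored, so the occurrence decision is not shielded from the investigator's attribution

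*Protocol*

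**What the plan says.** Section 6 places a safety review between cohorts. The reviewer is "a haematology specialist not linked to Araba University Hospital Haematology Department". The scope is wide: "This will involve an evaluation of all infusions performed", using the medical and nursing progress reports. The reviewer has two things to settle: "to determine whether a reaction has occurred and the grade thereof".

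The same paragraph gives the reason for masking: "In an attempt to minimise the influence of the investigator on the safety evaluation". The masking it then prescribes is that the reports reach the monitor after "references to the grade of the infusion-related reaction contained in the electronic medical records have been censored". No other part of the protocol masks anything further.

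Two other places bear on this. Sections 3.2.1 and 4.1 define an infusion-related reaction as an adverse event in the first 24 hours that is "considered to be related to infusion of the drug in the investigator's opinion". Section 7 says that the principal investigator or a designee "will be responsible for determining the possible relationship with the study treatment".

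**The concern.** The stated aim concerns the safety evaluation as a whole, and the monitor's first task is to say whether there was a reaction at all. The censoring protects only the second task, the grade. If a progress note says that a symptom was, or was not, an infusion reaction, the monitor reads that before deciding.

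Attribution is also the more exposed of the two judgements. By the protocol's definition, relatedness is a matter of opinion. Patients may receive chemotherapy after rituximab in the same session, so a symptom within 24 hours can have a competing explanation. The treating team knows the infusion rate, and Section 2.1 records its expectation that a faster rate should not affect safety. This is the ordinary situation for which masked review exists and is no criticism of the team.

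At stake is the decision to move to the next cohort. If the unmasked team tends to attribute events to something else, and the monitor follows that reading, the tendency passes into the escalation decision.

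**Working it through.** **1. The monitor's tasks set against the masking**

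| Question for the monitor | Investigator's view censored? | Cohort rule that depends on it |
| --- | --- | --- |
| Did a reaction occur? | No: neither the reaction label nor a causality statement is mentioned | Count rule, and the grade 2 or higher stop |
| What was its grade? | Yes | Grade 2 or higher stop |

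The grade stop appears in both rows because an event must be called an infusion-related reaction before its grade can trigger the rule. The first row is unprotected, and both rules pass through it.

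Section 6 words the count in two ways: its opening text counts mild to moderate reactions, and the group descriptions count infusion-related reactions without that limit. The argument is the same for either.

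**2. The plan's own figures**

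- Threshold: 4/16 = 25.0%, as Section 6 states.
- Total: 3 × 16 = 48 infusions, as Section 8.1 states.
- One reclassified event moves a cohort from 4/16 = 25% (stop) to 3/16 = 18.75% (proceed).

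**3. Illustration of sensitivity**

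From Section 6: n = 16, and a cohort passes the count rule with three or fewer reactions. Assumed, because the protocol gives no figure: a true reaction rate p = 25%, and a share m of true reactions not counted because a not-related reading is carried over (m = 0, 1 in 10, 1 in 5). Infusions are treated as independent.

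Count rule alone, with r = p(1 − m):

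P(pass) = Σ C(16,k) r^k (1 − r)^(16−k), for k = 0 to 3

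- m = 0, r = 0.250: 0.0100 + 0.0535 + 0.1336 + 0.2079 = 0.405
- m = 1/10, r = 0.225: 0.0169 + 0.0787 + 0.1713 + 0.2321 = 0.499
- m = 1/5, r = 0.200: 0.0281 + 0.1126 + 0.2111 + 0.2463 = 0.598

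Grade 2 or higher stop alone, assuming a true rate of 5%:

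- m = 0: (1 − 0.05)^16 = 0.440
- m = 1/5: (1 − 0.04)^16 = 0.520

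Both rules together, if 5 points of the 25% are grade 2 or higher and 20 points are grade 1. Passing needs no grade 2 or higher reaction and at most three of grade 1:

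P(pass both) = Σ C(16,k) [0.20(1 − m)]^k [1 − 0.25(1 − m)]^(16−k), for k = 0 to 3

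- m = 0: 0.0100 + 0.0428 + 0.0855 + 0.1064 = 0.245
- m = 1/10: 0.308
- m = 1/5: 0.379

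**4. What the text does and does not establish**

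The protocol states that grade references are censored. It does not state that the reports contain the investigator's relatedness judgement. That such a judgement would be visible follows from the censoring being limited to grade.

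**The case against.** A reader might infer that the monitor is not independent, so that the escalation gate is only the investigator's opinion at second hand. The protocol does not support that. The monitor comes from outside the department, reviews every infusion and not only flagged ones, and reads nursing as well as medical reports. Such a monitor can count a reaction that nobody labelled. The protocol also promises only an attempt to minimise influence. This objection stands: the defect is that the decision is unshielded, not that the monitor lacks independence.

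A reader might also infer that a deleted grade tells the monitor which events the investigator classed as reactions. That needs the deletion to leave a trace and every labelled reaction to carry a written grade. Section 6 does not describe how the censoring is done, so this is a possibility and not a finding.

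Third, wider redaction would not fully hide the investigator's call. Section 6 returns a patient with a reaction to the standard rate, and treatments given stay in the record. This stands too: the change reduces influence and does not remove it.

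Fourth, the magnitudes rest on assumed miss rates that run in one direction. Visible labels could equally lead the monitor to accept doubtful events as reactions. The count-rule figures also overstate the overall chance of proceeding, because the grade stop applies as well and grade is the item that is masked. All of this stands, and the figures show sensitivity only.

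Fifth, under Sections 3.2.1 and 4.1 the investigator's opinion is part of the definition of the event. Removing causality statements would take away a defining element unless the protocol says that the monitor's judgement serves for the cohort decision. This is correct and shapes the fix.

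None of these answers the central point: the masking rule is narrower than the purpose given for it in the same sentence.

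**Conclusion.** The point holds as a gap in a safeguard that the protocol itself specifies. The monitor is asked two questions, the stated masking covers one, and the unmasked one feeds both cohort rules. This is not detail that a protocol would leave to an analysis plan, because Section 6 fixes the masking step and fixes it too narrowly.

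The certain part of its size is that one event separates proceeding from stopping under the count rule. Beyond that, at the assumed 25% rate the chance of passing the count rule alone is 40.5% with nothing missed, 49.9% with 1 in 10 missed and 59.8% with 1 in 5 missed. For both rules together, under the assumed 5-point split, it is about 24%, 31% and 38%. These are not estimates of bias in this trial. The conclusion also supposes that progress reports carry some statement of attribution, which is inferred and not stated.

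The change is worth making before the first cohort review. The trial can run without it.

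**What to change.** In Section 6:

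- Extend the existing censoring to the investigator's reaction label and any causality statement, as well as grade.
- Apply it in the same way to the reports of all 16 infusions in each cohort, including those recorded as uneventful.
- Leave signs, symptoms, onset times, vital signs, interruptions and treatments visible, so that the monitor has what is needed to judge.
- State that the monitor's own judgement of occurrence, relatedness and grade is the one used for the cohort decision. Reconcile this with the definition by investigator opinion in Sections 3.2.1 and 4.1, for example by saying which determination serves the cohort decision and which serves the reported endpoint.

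The last item is needed for the others to work. The cost is somewhat more editing of free text in a redaction step that already exists, with care not to remove clinical context. No extra assessor is needed, and no treatment or stopping rule changes.

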**4.5.- Biases and limitations of the study**

The pilot study proposed does not have a sufficient sample size to demonstrate statistically significant differences in the percentage of infusion-related reactions that may occur in each study group compared with the percentage of infusion-related reactions that occur in standard treatment with rituximab at the standard rate (i.e., 400 mg/h). However, as the maximum infusion rate described in the scientific literature is 60 min, the present study appears to be the first to evaluate the safety with ultrarapid infusion rates of 30 min. As such, despite lacking sufficient power, it has been decided to perform an initial pilot study to evaluate the safety of ultrarapid infusions before carrying out a subsequent multicentre clinical trial.

Given the escalation nature of the study, patients will not be assigned randomly to the three study groups and, if they do not suffer any adverse infusion-related reaction, the same patient may receive the infusions described for the three study groups. This may bias the results as the characteristics of the patient and the type of lymphoma they suffer may affect the percentage of infusion-related reactions that occur with each infusion type to be studied. However, and despite the small sample size, the intention is to analyse infusion-related reactions based on the characteristics of the disease.

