# 5.- SUBJECT SCREENING AND WITHDRAWAL

Inclusion criteria:

- Patients who have tolerated the maximum intravenous administration rate for rituximab (400 mg/h) during the first or second infusion.
- The last infusion of rituximab must have taken place in the previous 3 months.
- All patients receiving rituximab may be included irrespective of whether they do so as monotherapy or in combination with chemotherapy and irrespective of the line in which they are receiving it.
- Patient in both induction and maintenance treatment will be included.
- All patients must sign the informed consent.

Exclusion criteria:

- Patients with an initial absolute lymphocyte count >10x10^3^ cells/µL.
- Patients who have presented hypersensitivity and serious adverse effects (grade 2 or higher) after the first or second infusion.
- Severe heart failure (NYHA class III-IV) or severe uncontrolled heart disease.
- Respiratory failure, uncontrolled COPD/severe asthma.
- Patients allergic to the premedication: paracetamol or polaramine.
- Severe active infection.
- Pregnant patients. *
- Refusal to participate

* For patients of child-bearing age (women of child-bearing age are considered to be those between menarche and post-menopause, except for those who are permanently sterile), a pregnancy test must be performed prior to treatment.

Women of child-bearing age participating in the trial must use effective contraceptive methods during treatment and for up to 12 months afterwards. These methods include:

- - - Sexual abstinence.
    - Female sterilisation.
    - Sterilisation of the (male) partner.
    - Intra-uterine device (IUD)

Withdrawal criteria:

- Onset of one or more grade 2 or higher infusion-related reactions
- The presence of four or more mild to moderate infusion-related reactions (25%) in the 16 patients of the corresponding cohort

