    - Subsequent 50 minutes at 720 mg/hour

A total of 16 infusions will be included in this group and the safety thereof will be evaluated. If the number of AEs is not higher than normal (more than three infusion-related reactions), the second intervention will commence. In the event that the number of infusion-related reactions is higher than in standard clinical practice, the study will be suspended without continuing with the following groups.

ULTRARAPID INFUSION GROUP

Administration of the IV premedication half an hour prior to the infusion of rituximab as per the standard regimen; generally, dexchlorpheniramine 5 mg IV and paracetamol 1 g IV half an hour prior to rituximab.

The rituximab dose will then be administered at the standard dose: 375 mg/m^2^ diluted in 250 mL of saline over half an hour, as follows:

- - - First 10 minutes at 450 mg/hour.
    - Subsequent 20 minutes at 1800 mg/hour.

A total of 16 infusions will be included in this group and the safety thereof will be evaluated. If the number of infusion-related reactions is not higher than normal (more than three infusion-related reactions), the third intervention will commence. In the event that the number of infusion-related reactions is higher than in standard clinical practice, the study will be suspended without continuing with the following group.

ULTRARAPID PLUS INFUSION GROUP

Administration of the oral premedication half an hour prior to the infusion of rituximab as per the standard regimen for administration of subcutaneous rituximab: dexchlorpheniramine 4 mg orally and paracetamol 1 g orally half an hour prior to rituximab.

The rituximab dose will then be administered at the standard dose: 375 mg/m^2^ diluted in 250 mL of saline over half an hour, as follows:

- - - First 10 minutes at 450 mg/hour.
    - Subsequent 20 minutes at 1800 mg/hour.

A total of 16 infusions will be included in this group and the safety thereof will be evaluated. This ultrarapid infusion regimen will be considered to be safe if the number of infusion-related reactions is three or less.

Safety will be evaluated by monitoring infusion-related reactions, including all haematological and non-haematological serious and non-serious adverse events related to the study drugs. If an infusion-related reaction occurs, the standard administration rate of 400 mg/h will be used.

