# 8.- STATISTICS

## 8.1.- Sample Size

The expected number of infusions is 48, distributed into 16 infusions per group. It is recommended to include between 30 and 50 measurements in a pilot study^18,19^.

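### The escalation rule counts 16 patients but the cohorts are filled with 16 infusions, and only non-reactors may re-enter, so faster cohorts can look safer than they are

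*Protocol*

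**What the plan says.** **Unit of the safety rule.** Protocol section 6 calls a cohort safe "if fewer than four mild to moderate infusion-related reactions occur in the 16 patients from the corresponding cohort (25% of reactions"). The withdrawal criteria in section 5 repeat the limit as "four or more mild to moderate infusion-related reactions (25%) in the 16 patients of the corresponding cohort". Both count patients.

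**Unit of the cohort.** The description of each of the three groups in section 6 says "A total of 16 infusions will be included in this group and the safety thereof will be evaluated", and continuation depends on three or fewer reactions among them. Section 8.1 agrees: "The expected number of infusions is 48, distributed into 16 infusions per group". It justifies the total only by a rule of thumb: "It is recommended to include between 30 and 50 measurements in a pilot study". These places count infusions.

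**Re-entry.** Section 4.5 states that assignment is not random and that "if they do not suffer any adverse infusion-related reaction, the same patient may receive the infusions described for the three study groups". It accepts that this may bias the results through patient and lymphoma characteristics, and its response is that "the intention is to analyse infusion-related reactions based on the characteristics of the disease". Section 5 withdraws patients with a grade 2 or higher reaction, and section 6 returns a reacting patient to the standard rate.

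**Analysis.** Section 8.2 names chi-squared or Fisher tests, Student's t or Mann–Whitney tests, and Kaplan–Meier. It names no paired or clustered method.

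**The concern.** There are three linked problems.

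1. **The denominator is undefined.** The count out of 16 decides whether the next cohort opens. If several infusions may come from one patient, 4 of 16 is a rate per infusion and not the patient rate that sections 5 and 6 describe.
2. **Re-entry is selective.** A patient carried into a faster cohort has, by definition, already tolerated a slower one. If patients differ in susceptibility, the later cohorts hold more tolerant patients. The bias then runs towards apparent safety, in the 30-minute groups that section 4.5 presents as the new question.
3. **The tests assume independent groups.** Patients shared between cohorts break that assumption.

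At stake is whether a pass in cohort 2 or 3 says something about the infusion rate or about who was left to receive it.

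**Working it through.** **The plan's own figures.** 3 × 16 = 48 infusions and 4/16 = 25%; both reproduce. There is no power calculation to check. The 48 infusions are 48 patients only if nobody contributes twice. With one infusion per patient per cohort and full re-entry, 16 patients would supply all 48.

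**Assumptions.** The protocol gives no reaction risk and no within-patient correlation. I take a constant true risk p = 25% (the protocol's own threshold) in all cohorts, with patient propensity following a beta distribution with mean p and ICC ρ of 0, 0.3 or 0.5.

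**Step 1: the unit.** Suppose 8 patients supply two infusions each. Three reacting patients meet the rule of three or fewer, yet 3/8 = 37.5% of patients reacted. With 16 distinct patients the same count is 3/16 = 18.75%.

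**Step 2: selection.** Mean risk after one clean infusion is p(1 − ρ). After two it is p(1 − ρ)/(1 + ρ). The chance of passing is P(X ≤ 3) for X ~ Binomial(16, risk).

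| ρ | Cohort 1 | Cohort 2, all carried over | Cohort 3, all carried over |
|---|---|---|---|
| 0 | 25%: 0.41 | 25%: 0.41 | 25%: 0.41 |
| 0.3 | 25%: 0.41 | 17.5%: 0.70 | 13.5%: 0.84 |
| 0.5 | 25%: 0.41 | 12.5%: 0.87 | 8.3%: 0.96 |

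The all-carried-over columns are a limiting case. With one infusion each, 16 carried-over patients require no reactor in cohort 1, which at 25% has probability 0.75^16 = 0.01. If reactors are instead replaced by new patients, the mean risk in cohort 2 is (1 − p) × p(1 − ρ) + p × p:

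- ρ = 0.3: 0.75 × 0.175 + 0.25 × 0.25 = 19.4%, chance of passing 0.62.
- ρ = 0.5: 0.75 × 0.125 + 0.25 × 0.25 = 15.6%, chance of passing 0.77.

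At a lower assumed risk of 10%, carried-over patients show 7.0% then 5.4% (ρ = 0.3), or 5.0% then 3.3% (ρ = 0.5).

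**Step 3: standard error between cohorts.** For independent groups the standard error of the difference is √(2p(1 − p)/16) = √(2 × 0.25 × 0.75/16) = 0.153. If the same 16 patients are in both cohorts once each, and leaving selection aside, it is √(2p(1 − p)(1 − ρ)/16) = 0.128 at ρ = 0.3 and 0.108 at ρ = 0.5. The unpaired test therefore uses a standard error that is too large.

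**Step 4: precision within a cohort.** This applies only if patients repeat within a cohort. For no events in n independent units, the two-sided 95% exact upper limit is 1 − 0.025^(1/n).

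- n = 16: 20.6%.
- n = 8: 36.9%.

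For 16 infusions from 8 patients, the limit on the risk per infusion lies between 20.6% (ρ = 0) and 36.9% (ρ = 1). At ρ = 0.5 the design effect is 1 + (2 − 1) × 0.5 = 1.5, the effective n is 16/1.5 = 10.7, and the approximate limit is 29.2%.

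**The case against.** The strongest reply is that 16 patients and 16 infusions together most simply mean one infusion per patient per cohort. Section 6 speaks of an appointment for the treatment cycle in the singular, and section 4.5 allows re-use across groups without mentioning repeats within one. That is a reasonable reading, but no sentence fixes it, and the count governs escalation. Because reactors return to the standard rate, several reactions from one patient at the study rate are unlikely. Repeats would mostly add clean infusions to the denominator.

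It is also fair that section 4.5 admits bias and low power, and that escalation rests on counts and an external safety monitor, not on p-values. Since one grade 2 or higher reaction suspends the trial, a later cohort opens only with no earlier primary events, so the choice of test matters less than the selection. The disclosure, however, omits the direction of the bias. Analysis by disease characteristics does not deal with selection on earlier non-reaction.

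A reader might infer two stronger claims that the documents do not support:

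- **That re-entry makes the tests overstate precision.** Between cohorts the reverse holds (step 3). Overstated precision needs repeats within a cohort, which the text neither states nor excludes, or pooling 48 infusions as 48 patients.
- **That repeats simply widen the limit from 20.6% to 36.9%.** The second figure is a limit on the risk per infusion only at ρ = 1. Under independence, 1 − (1 − 0.206)² = 36.9% is the same bound restated as the risk over two infusions.

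**Conclusion.** The concern holds in this form and should be fixed. The protocol contradicts itself on the counting unit of its escalation rule, and it lets only non-reactors carry forward. At a constant 25% risk, selection alone would raise the chance of passing cohort 2 from 0.41 to between 0.62 and 0.77 with reactors replaced, or to between 0.70 and 0.87 if everyone is carried over. In a cohort 3 wholly carried over it would reach 0.84 to 0.96. These sizes rest on the assumed risk and an assumed ICC of 0.3 to 0.5. The direction needs only that patients differ in susceptibility; at ICC 0 there is no effect. At a risk of 10% the shift in a wholly carried-over cohort 2 is small in absolute terms: from 16 × 0.10 = 1.6 expected reactions to 16 × 0.07 = 1.1 or 16 × 0.05 = 0.8. The unpaired tests in 8.2 do not fit overlapping patients, but their fault is a wrong standard error on a selected sample, not general overconfidence.

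**What to change.** **Sections 5, 6 and 8.1.** Reconcile the passages on one counting unit. Count each patient once per cohort: the numerator is patients with at least one qualifying reaction, and the denominator is patients infused. This settles only the unit. What the threshold should be, and which reactions qualify, remain for the sponsor.

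**Section 8.2.** Drop the unpaired between-cohort tests where patients overlap. Report each cohort descriptively with exact intervals, giving numbers of patients and of infusions, separately for newly enrolled and carried-over patients and by rituximab cycle number, which section 4.1 already collects. McNemar's test is not a substitute. Patients who reacted earlier do not re-enter, so the cell for reacted earlier but not later is empty by design and the test could only point towards an increase.

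**Section 4.5.** State the direction of the selection bias. Limit any conclusion that rests on carried-over patients to patients who tolerated the preceding rate.

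**Cost.** Protocol wording and a little more tabulation. Accrual may be slightly slower, and the intervals for newly enrolled and carried-over patients will be wider than for a whole cohort.
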